#### Staff-centered secondary outcomes

The staff-centered secondary outcomes include sick-related absence during T2, as well as self-reported data on employees’ attitudes towards their work situation that are relevant to patient safety (i.e., dealing with errors, team cooperation, team communication, and management) during T1 and T2. Self-report data will be obtained with the German version of the Safety Attitudes Questionnaire [14] and will consist of 27 items that have been partly modified to be appropriate for the study context.

### Participant timeline {13}

Participant enrolment, intervention implementation, and assessments will follow a fixed timeline as illustrated in Fig. 4.

**Fig. 4 Fig4:**
[figure not shown]
Study timeline. *t_o_ = baseline; t_1_ = 1 month after study start (implementation of ICU Support in the intervention arm); t_2_ = 4 months after study start. ** IC complications [number] = number of intensive care complications according to Clavien-Dindo classification scheme; IC complications [severity] = average severity of intensive care complications according to Clavien-Dindo classification scheme; Sick-related absence [ICU staff] = amount of sick-related leave hours of ICU staff relative to the amount of planned working hours; SAQ = Safety Attitudes Questionnaire (German version)

### Sample size {14}

Sample size calculations were performed with the statistical software G*Power software version 3.1.9.7 [15] and were based on the respective primary outcome parameter.

#### ICU patients

An analysis of covariance (ANCOVA; fixed effects, main effects, and interactions) with two groups, two measurement times (T0 and T1), and 4 covariates (age, sex, previous illnesses, and length of stay) was scheduled to calculate the appropriate sample size. Assuming a small effect of *f* = 0.10 according to Cohen (1988) [16], an alpha error level of 0.05 and a power of 90%, the total sample size was *N* = 1053. To account for an expected dropout of 10%, a total number of 1110 patients will be targeted.

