#### ICU staff

The sample size calculation for the staff-centered outcomes was based on the relative risks (RR) of the two groups (intervention/control) for the measurement times T0 and T1. A small effect of RR = 1.22 according to Olivier et al. (2017) was assumed [17], an average work loss of 2.5% before the intervention, an alpha error level of 0.05, and a power of 90%. This resulted in a total sample of *N* = 37,484 h per time point. Assuming a dropout of 10%, a total number of *N* = 293 employees will be targeted.

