### Recruitment {15}

The selection of the centers is based on a previous research project, in which several of the centers participated, as well as via personal contacts. The centers are widely distributed over Germany, located in six different states (North-Rhine Westphalia, Rhineland-Palatinate, Schleswig–Holstein, Bavaria, Saxony, and Berlin). There was no minimum criterion for inclusion, except for the existence of an ICU.

The sample size calculation (please see {14}) was done entirely independently from the center recruitment and based on statistical literature. Since previous literature on similar interventions is scarce (particularly in combination with the outcome variables), it was not possible to derive empirically supported effect size estimates. Therefore, we decided for rather conservative estimates of small effect sizes.

Considering the temporal sequence, sample size planning was performed after the center recruitment. Nonetheless, it was an essential precondition for study initiation since it indicated whether the study was possible at all. As for the patient sample, the duration of the data acquisition periods was defined based on previous data on patient numbers in the respective centers. Data acquisition periods were planned for a duration assuring a sufficient number of patients. As for the employee data, we had no influence on the number of employees; however, we were able to assess the total number of employees (1.066 persons), which was more than three times the required number. There is no expected dropout since the data are collected anonymously via the HR departments, which have complete records about the entire staff.

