## Statistical methods

### Statistical methods for primary and secondary outcomes {20a}

Data will be analyzed with IBM SPSS Statistics software version 25 (IBM Corp., Armonk, NY, USA). To analyze the effect of the ICU Support intervention on the patient-centered primary outcome, an analysis of covariance with time as the within-subject factor (T0 and T1), study group as the between-subject factor (intervention and control), and 4 covariates (age, sex, previous illnesses, and length of stay) will be conducted. Significance will be determined by two-sided 95% confidence intervals.

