### Methods in analysis to handle protocol non-adherence and any statistical methods to handle missing data {20c}

No such methods are planned or intended. The only data relying on participant's protocol adherence is questionnaire data. All other data are regularly collected by the hospitals during their everyday working routine (either for treatment or for staff management). For these data, no missing data points are expected.

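### The patient target of 1110 does not contain the stated 10% dropout allowance on 1053; it allows about 5% (minor, wrong as written)

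*Protocol article*

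**What the plan says.** Sample size {14}, ICU patients, plans an analysis of covariance with two groups, two measurement times and four covariates. It assumes a small effect of f = 0.10 and continues with "an alpha error level of 0.05 and a power of 90%, the total sample size was *N* = 1053". The next sentence reads: "To account for an expected dropout of 10%, a total number of 1110 patients will be targeted".

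Three other sections bear on whether patients can be lost at all. Outcomes {12} says that patient outcomes are taken retrospectively from patient records. The retention section {18b} says that data other than the survey do not depend on patients or employees taking part. Section {20c} says of data collected in hospital routine, for treatment or staff management: "For these data, no missing data points are expected".

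For staff, Sample size {14}, ICU staff, has "Assuming a dropout of 10%, a total number of" 293 employees, whereas Recruitment {15} says: "There is no expected dropout since the data are collected anonymously via the HR departments".

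**The concern.** The target should equal the required number inflated for the stated loss, and 1110 is visibly too close to 1053 for a 10% allowance. Either the loss rate or the target is misstated, and the reader cannot tell which. At stake is whether the stated target delivers the 1053 evaluable patients, and hence the 90% power, that the same paragraph claims. A second question is why any dropout is expected for outcomes read from routine records. The staff paragraph raises that question more sharply, because Recruitment {15} denies any dropout for the same HR data.

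**Working it through.** **Inputs.** From Sample size {14}, ICU patients: f = 0.10, alpha 0.05, power 90%, N = 1053, dropout 10%, target 1110, 2 groups × 2 times = 4 cells, 4 covariates. From Statistical methods {20a}: "Significance will be determined by two-sided 95% confidence intervals". One assumption is added: numerator degrees of freedom df1 = 1, which the text does not give but which reproduces its figure.

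**Step 1: reproduce 1053.** Use the noncentral F distribution with λ = f² × N and df2 = N − 4 − 4.
- At N = 1053: λ = 0.01 × 1053 = 10.53, df2 = 1045, power = 0.9001. This is the smallest N that reaches 90%.
- The result is also 1053 with 2 groups or without covariates. The normal approximation with a standardised difference of 0.20 gives 1052. With df1 = 3 the answer would be 1422, so df1 = 1 was evidently used.

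The base figure is therefore correct on its own terms, and the discrepancy lies in the inflation step.

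**Step 2: inflate for 10%.**
- N/(1 − d) = 1053/0.90 = 1170, which is 60 more than 1110.
- N × (1 + d) = 1053 × 1.10 = 1158.3, so 1159, which is 49 more than 1110.

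Neither usual formula gives 1110, and the gaps are too large for rounding.

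**Step 3: what loss does 1110 allow?**
- 1 − 1053/1110 = 57/1110 = 5.1%. On the cruder formula, 1110/1053 − 1 = 5.4%.
- For comparison, a 5% allowance gives 1053/0.95 = 1108.4, so 1109, or 1053 × 1.05 = 1105.65, so 1106.

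The target fits about 5%.

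**Step 4: consequence for power, in the same model.**

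| Loss from 1110 | Patients left | λ | Power |
|---|---|---|---|
| none | 1110 | 11.10 | 91.4% |
| 57 patients (5.1%) | 1053 | 10.53 | 90.0% |
| 10% | 1110 × 0.90 = 999 | 9.99 | 88.4% |

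The worst case is a drop of 0.9001 − 0.8845 = 0.0156, about 1.6 percentage points.

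**Step 5: staff.** 293 employees includes a 10% allowance. Taking it out gives roughly 293 × 0.90 = 264 or 293/1.10 = 266. Recruitment {15} counts 1,066 employees, and 1066/293 = 3.6, so the staff requirement is met with or without the allowance.

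**The case against.** The strongest reply is that little follows from the error, and most of that reply stands.

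- **The shortfall is conditional.** It arises only if 10% of patients are really lost. If section {20c} is right and none are, 1110 exceeds 1053. A reader might infer that the trial is underpowered because of this sentence; the documents do not support that.
- **The windows.** A reader might also infer that 1110 fixed the length of the data collection periods. Recruitment {15} says only that the periods were based on earlier patient numbers at the centers and chosen to give enough patients. It does not name 1110, and collection runs in fixed 45-day periods with no stop at that number. Whether the periods yield too few patients cannot be told from this document.
- **A misprint is possible.** 1110 and 1170 differ by one digit. If 1170 was meant, only the printed text is wrong. This cannot be confirmed here.
- **The meaning of dropout.** It could refer to patients removed after identification, for example those transferred between study sites, whom the eligibility criteria exclude. The article does not say so. This leaves tension with {20c} rather than a proven contradiction, and it does not rescue the arithmetic: a 10% loss of any kind still needs 1159 to 1170.
- **Scope of the Recruitment sentence.** Its statement that no dropout is expected concerns HR staff data. It contradicts the staff paragraph and cannot be used against the patient figure.
- **Scale.** Recruitment {15} concedes that no empirically supported effect size was available. Beside that uncertainty, 1.6 points of power is minor.

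What the reply does not remove is that three numbers in one paragraph disagree. That is an error in what is stated, not detail left to another document.

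**Conclusion.** The point holds as a minor error in the text. The stated target falls 60 patients short of a 10% allowance (49 on the cruder formula) and covers about 5%. Power would be 88.4% if 10% were lost and 91.4% if none were. These values rest on df1 = 1, f = 0.10 and the plan's own treatment of patients as independent; whether that treatment suits randomization by center is a separate question. The 10% patient dropout is in tension with the sections on routine records and missing data, but dropout is undefined. The staff paragraph and Recruitment {15} do contradict each other on the same HR data, without practical effect.

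**What to change.** Restate the sentence under Sample size {14}, ICU patients, so that rate and target agree. Any one of these would do:
- 1170 patients, allowing for 10% loss;
- 1110 patients, allowing for about 5% loss;
- 1053 patients required, no loss expected, which is the version consistent with {20c}.

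If a loss is kept, say in a few words what counts as dropout for patients whose data come from routine records. Separately, either remove the 10% from the staff paragraph or align Recruitment {15} with it.

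The cost is one corrected sentence in each of the two sample size paragraphs. Trial status reports that data collection is under way; the correction needs no new enrolment and does not touch the analysis.

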#### ICU staff

The sample size calculation for the staff-centered outcomes was based on the relative risks (RR) of the two groups (intervention/control) for the measurement times T0 and T1. A small effect of RR = 1.22 according to Olivier et al. (2017) was assumed [17], an average work loss of 2.5% before the intervention, an alpha error level of 0.05, and a power of 90%. This resulted in a total sample of *N* = 37,484 h per time point. Assuming a dropout of 10%, a total number of *N* = 293 employees will be targeted.

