#### Staff-centered primary outcome

Sick-related absence data for ICU staff will be obtained anonymously at the unit level via the HR department of the participating study center. To make this data comparable across study centers, we assessed sick-related absence as the amount of sick-related leave hours relative to the amount of planned working hours during T1.

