#### T1

Data collection period T1 will start 1 month after the start of the study and will last for 45 days. Equivalent to T0, patient-centered data will be collected during the first 45 days of T1, and sickness-related absence will be obtained during the first 30 days. Questionnaire data will be collected during the last 14 days of T1.

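### The staff sample size treats every working hour as independent although nine whole centres are randomised, so the stated 90% power, the 293 employees and the threefold surplus are unsupported

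*Protocol article*

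**What the plan says.** The ICU staff paragraph of Sample size {14} builds the calculation on "A small effect of RR = 1.22", "an average work loss of 2.5% before the intervention", and "an alpha error level of 0.05, and a power of 90" per cent. The result is "37,484 h per time point". After a 10% dropout allowance this becomes a target of 293 employees.

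Under Recruitment {15}, the total staff of the participating units is given as 1,066, "which was more than three times the required number". The same section describes sample size planning as a precondition for starting the study.

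Two other sections describe the design that this figure has to serve. Sequence generation {16a} randomises the nine centres, four to intervention and five to control. Staff-centered primary outcome says that "Sick-related absence data for ICU staff will be obtained anonymously at the unit level via the HR department", with sick hours expressed relative to planned hours in T1. Neither the sample size section nor the recruitment section mentions a design effect, an intracluster correlation or a centre term.

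**The concern.** A sample size counted in hours is valid only if hours carry independent information. Two features of this trial work against that. Each employee contributes roughly 140 planned hours to a 30-day window, and a sick employee can be expected to miss whole shifts rather than scattered hours. In addition, the intervention is allocated to whole centres, so any stable difference in absence between ICUs enters the comparison of arms directly. More hours from the same nine units do not reduce that component.

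At stake is the credibility of one of the two primary outcomes. As written, the protocol tells readers that the staff comparison is powered at 90% with a large reserve. An inconclusive result would then look more informative than it is.

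**Working it through.** **Inputs from the protocol.** Baseline loss 2.5%; RR 1.22, so the comparison rate is 0.025 × 1.22 = 0.0305; alpha 0.05; power 90%; dropout 10%; 293 employees targeted; 1,066 available; nine centres, four against five. Two-sidedness is stated in Statistical methods {20a}, in the paragraph on the patient outcome ("Significance will be determined by two-sided 95% confidence intervals"), and it is also what reproduces the staff figure.

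**Reproducing 37,484 h.** Pooled two-proportion formula, no continuity correction, equal arms, mean rate 0.02775:

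n per arm = [1.960·√(2·0.02775·0.97225) + 1.282·√(0.025·0.975 + 0.0305·0.9695)]² / 0.0055² = 18,741.04, rounded up to 18,742. Twice that is 37,484, an exact match. One-sided testing would give 30,550 and a continuity correction 38,206. The sampling unit is therefore the hour, with a design effect of 1 and no centre term.

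**Hours available.** 37,484 / 0.9 / 293 = 142.1 h per employee. All 1,066 employees give about 151,500 h, or 4.0 times 37,484. By headcount, 1,066 / 293 = 3.6.

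**Step 1: correlation within employee only.** Divide the hours by an assumed design effect (DE) and recompute the power of the same test. The documents give no spell length. DE 8 corresponds roughly to absence in single eight-hour shifts, and DE 24 to about three shifts.

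| DE (assumed) | Power at 37,484 h | Power with all 1,066 employees |
|---|---|---|
| 1 | 90% | above 99% |
| 4 | 37% | 90% |
| 8 | 21% | 63% |
| 24 | 10% | 26% |

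The surplus of staff absorbs a DE of about 4 and no more. Keeping 90% at DE 8 would need 8 × 37,484 = 299,872 h, about 2,110 employees.

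**Step 2: nine unit rates.** Take equal unit sizes, m = hours / 9, and a between-unit coefficient of variation (CV), also assumed. The variance of one unit's rate is p(1−p)·DE/m + (CV·p)². Arms are compared by a t-test on 7 df (noncentral t).

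Example with all employees, DE 8, CV 0.1, m = 16,836, and five units at 2.5% against four at 3.05%:
- Unit variances are 1.158×10⁻⁵ + 0.625×10⁻⁵ = 1.783×10⁻⁵ and 1.405×10⁻⁵ + 0.930×10⁻⁵ = 2.335×10⁻⁵.
- Standard error = √(1.783×10⁻⁵/5 + 2.335×10⁻⁵/4) = 0.00307.
- Noncentrality = 0.0055 / 0.00307 = 1.79. With critical t = 2.365, power is 34%.

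Giving the higher rate to the five units instead of the four changes results by at most about one percentage point, so ranges are shown. For T0 adjustment the variances are multiplied by 1 − 0.7² = 0.51 (assumed T0–T1 correlation 0.7, 6 df, critical t = 2.447).

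| All 1,066 employees, DE 8 | CV 0 | CV 0.1 | CV 0.2 |
|---|---|---|---|
| Unadjusted, 7 df | 50–51% | 34–35% | 19% |
| T0-adjusted, 6 df | 76–77% | 56–57% | 30–31% |

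A correlation of 0.7 is generous at CV 0, where T0 has little stable difference between units to predict.

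**Best case for the protocol.** At the planned 37,484 h, with independent hours and no between-unit variation, the unadjusted nine-unit t-test has 78–79% power; CV 0.2 alone brings this to 21–22%. With all 1,066 employees and independent hours, unadjusted power stays at 90% only if the CV is about 0.06 or less.

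**The case against.** The strongest reply is that the size of the loss rests on quantities that the documents do not contain. That is correct. Spell length, between-unit variation and the T0–T1 correlation are all assumed here, and at DE 4 without centre variation the full staff would still give 90%. Baseline adjustment also recovers a good part of the loss. Nothing in the protocol shows that these favourable conditions hold, however, and its calculation does not invoke them.

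A reader might infer more than the text supports in four places.

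- **Inflated false-positive rate.** It is tempting to say that the trial will test hours as if independent and so reject true nulls far too often. Statistical methods {20a} gives a model for the patient outcome only. The relative risk appears for staff in the sample size alone, and the analysis plan is not shown. The documents support an unsupported power statement, not a demonstrated faulty test.
- **Near-perfect correlation of an employee's hours.** With about 142 h per employee that would mean a DE near 142. The values used here imply far less: (8 − 1)/141 = 0.05 and (24 − 1)/141 = 0.16.
- **Only one ratio per unit.** The protocol says that data are obtained at unit level. It does not say that HR supplies a single total and nothing finer.
- **The 30-day window.** The rule that "sickness-related absence will be obtained during the first 30 days" matches T0 and is not an error. Trial status reports the intervention as implemented in both groups, so T1 has ended; lengthening the window now would redefine a primary outcome after the fact.

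It is also true that the investigators had no influence on staff numbers, so no recruitment decision turns on this figure. The adequacy claim is still printed and will be relied on.

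**Conclusion.** The point stands as a fault in the stated sample size. That 37,484 h is an independent-hours calculation is established by exact reproduction, and that nine centres are the randomised units is stated in the protocol. Neither depends on an assumption. It follows that the 90% power, the 293 employees and the threefold surplus do not describe this design.

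The size is conditional. Over DE 4 to 24 without centre variance, power with all staff runs from about 90% down to 26%. At DE 8 with between-unit CV 0 to 0.2, it is about 51% to 19% unadjusted and about 76% to 31% with T0 adjustment. These ranges illustrate plausible losses and do not estimate the trial's actual power.

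**What to change.** Define the staff analysis at the level of randomisation. For each of the nine units, compute sick hours divided by planned hours at T1 and compare arms with the unit's T0 proportion as covariate. Use a t reference on 6 df, or a permutation test over the 9!/(4!·5!) = 126 ways of allocating four of nine centres.

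Withdraw the statements on 37,484 h, 293 employees, 90% power and more than three times the required number. In their place report the difference that nine units can detect, taking the between-unit variance from the T0 unit proportions.

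The cost is wording in the protocol and analysis plan plus one calculation on T0 data that HR already holds. No new data are needed. The price is a stated power much less favourable than 90%.

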### Recruitment {15}

The selection of the centers is based on a previous research project, in which several of the centers participated, as well as via personal contacts. The centers are widely distributed over Germany, located in six different states (North-Rhine Westphalia, Rhineland-Palatinate, Schleswig–Holstein, Bavaria, Saxony, and Berlin). There was no minimum criterion for inclusion, except for the existence of an ICU.

The sample size calculation (please see {14}) was done entirely independently from the center recruitment and based on statistical literature. Since previous literature on similar interventions is scarce (particularly in combination with the outcome variables), it was not possible to derive empirically supported effect size estimates. Therefore, we decided for rather conservative estimates of small effect sizes.

Considering the temporal sequence, sample size planning was performed after the center recruitment. Nonetheless, it was an essential precondition for study initiation since it indicated whether the study was possible at all. As for the patient sample, the duration of the data acquisition periods was defined based on previous data on patient numbers in the respective centers. Data acquisition periods were planned for a duration assuring a sufficient number of patients. As for the employee data, we had no influence on the number of employees; however, we were able to assess the total number of employees (1.066 persons), which was more than three times the required number. There is no expected dropout since the data are collected anonymously via the HR departments, which have complete records about the entire staff.

## Assignment of interventions: allocation

### Sequence generation {16a}

The nine participating study centers were randomly assigned to the intervention or control arm prior to the start of the study, using a web-based randomizer [18]. Following this procedure, four study centers were assigned to the intervention arm and five study centers were assigned to the control arm.

